### Sample size

On the basis of the literature, an increase in bacterial growth of 100 colony-forming units (CFUs) per plate will be considered clinically significant [32]. For a statistical power of 95% and an alpha test risk of 5%, the sample size has been estimated to be 48 patients per study arm.

### Group assignment, randomization and allocation concealment

Patients will be randomly allocated to group I (n = 48), in which the dressing will be removed on the first postoperative day, or group II (n = 48), in which the dressing will be removed on the sixth postoperative day. Allocation will be determined by a random, computer-generated sequence (Bioestat 5.0, Instituto Mamirauá, Belém, PA, Brazil). An opaque envelope with the patient number will be opened on the first postoperative day to reveal the allocation of the patient.

### Procedures and interventions

Patients will be instructed to bathe before surgery with a 4% chlorhexidine-based detergent (Rioquímica Indústria Farmacêutica Ltda., São José do Rio Preto, Brazil) [33]. In the operating room, antisepsis of the surgical site will be performed with a 0.5% chlorhexidine solution in alcohol (Rioquímica Indústria Farmacêutica Ltda., São José do Rio Preto, Brazil) [34]. The nipple areola complexes will remain uncovered during the operation; sterile tapes will not be used to cover them, since this is not the standardized procedure in our hospital. Patients will undergo breast augmentation under general anesthesia. All patients will receive prophylactic antibiotics (cefazolin - União Química Farmacêutica Nacional S.A., São Paulo, Brazil) [35].

The surgical approach will be via the inframammary fold. Implants (Silimed Indústria de Implantes Ltda., Rio de Janeiro, Brazil) will be placed in the subglandular, submuscular or subfascial position, depending on which is the best course of action for a given patient. The surgical site will be cleaned with sterile saline after the surgery. A sample of skin flora will be obtained for semiquantitative culture before the application of a dressing over the surgical incision.

The dressing will consist of four layers of cotton gauze, covered with micropore tape. The surgical team will not know to which group the patient belongs. On the first postoperative day, the allocation envelopes will be opened. If the patient is allocated to group I, the dressing will be removed, and a sample will be harvested for culture. The patient will be instructed to return to their normal personal hygiene routine and return on the sixth day for reassessment and collection of samples for culture. If the patient is allocated to group II, she will be instructed to not wet the bandage for six days, when it will be removed and a sample will be harvested for culture. Thus, samples of the skin flora will be obtained in the operating room just before placement of the dressing and after removal of the dressing. Additional samples will be obtained on the sixth postoperative day from patients in group I.

### Method of sample collection

A sterile fenestrated paper field with a standard 5 cm per 10 cm area will be placed over the surgical wound on the right breast. A sterile swab soaked in sterile saline will be passed across the predetermined area in a standardized manner. This swab will be placed in a sterile tube containing 1.0 ml of sterile saline and immediately transferred to the laboratory.

Culture methodsStandard culture methods will be used for the identification of microorganisms [36]. Aliquots of 0.2 ml from each sample will be plated on agar medium hypertonic mannitol (HiMedia Laboratories Pvt. Ltd., Mumbai, India) to culture *Staphylococcus* sp., on blood agar (HiMedia Laboratories Pvt. Ltd., Mumbai, India) to identify hemolytic colonies, on eosin-methylene blue agar (HiMedia Laboratories Pvt. Ltd., Mumbai, India) to identify *Enterobacteriaceae*, and on Sabouraud agar supplemented with chloramphenicol (HiMedia Laboratories Pvt. Ltd., Mumbai, India) (0.05 mg/ml) to detect fungi. The plates will be incubated in an aerobic atmosphere at 37°C. After 48 hours, a microbiologist will assess the plates. The lab technicians and microbiologist will not know which group each sample belongs to.

Culture results will be expressed as CFUs per plate. When a result exceeds 300 CFUs, it will be recorded as ‘>300 CFU/plate’. Staphylococci will be identified as coagulase-negative staphylococci or *Staphylococcus aureus*, on the basis of the results of Gram staining, the presence of hemolysis, and the results of the coagulase test.

### Assessment of postoperative infections and dressing duration

Patients will be evaluated weekly for four weeks, and then re-evaluated at six months and one year after the operation. The CDC definition and classification of SSIs will be used. As the surgery involves the implantation of prostheses, an SSI is defined as an infection that occurs within one year after the surgery [37]. The patients will use a five-point scale to classify the dressing in terms of comfort, practicality and safety. This assessment will be done at the postoperative week two visit for each patient.

### Outcomes

The primary outcome will be cutaneous colonization, expressed as the number of CFUs. The incidence of SSI and the perceptions of patients towards healing will be secondary outcomes. Participation will be completed at one year after surgery, after evaluation for the presence of infection.

### Statistical analysis

The Mann–Whitney U test will be used to test the homogeneity of the groups in terms of age, BMI and duration of surgery. The Friedman test will be used to compare the number of CFUs in the samples collected before, and one and six days after the application of the dressing in group I. If there is a significant difference between these times, then the Friedman test will be supplemented with the multiple comparisons test to determine at which time points significant differences appeared. In group II, the Wilcoxon test will be used to compare the number of CFUs in samples collected before the dressing and on the sixth postoperative day. The Mann–Whitney U test will be used to compare groups I and II in terms of the number of CFUs before and six days after the application of the dressing. Tests will always be applied independently for each medium used.

The Fisher test will be used to compare groups I and II in terms of the rates of infection. The Kolmogorov-Smirnov test will be used to compare the two groups in terms of the perceptions of the patients regarding the comfort, safety and practicality of the dressings. All statistical analyses will be performed using SPSS software (version 18, SPSS Inc., Chicago, United States of America). A *P* value ≤0.05 will be considered to be statistically significant.

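### The change in CFUs from before the dressing to day 6 is tested by a gated Friedman procedure in group I but by a direct Wilcoxon test in group II, so the within-arm verdicts face unequal hurdles; the randomised day-6 comparison is unaffected

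*Protocol article*

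**What the plan says.** All of the tests are in the Statistical analysis section of the protocol article.

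- **Group I, three time points:** "The Friedman test will be used to compare the number of CFUs in the samples collected before, and one and six days after", counted from when the dressing goes on.
- **Group I, pairwise step, taken only if that result is significant:** "the Friedman test will be supplemented with the multiple comparisons test to determine at which time points significant differences appeared". The procedure is not named.
- **Group II, two time points, no gate:** "In group II, the Wilcoxon test will be used to compare the number of CFUs in samples collected before the dressing and on the sixth", meaning day 6 after surgery.
- **Between groups:** "The Mann–Whitney U test will be used to compare groups I and II in terms of the number of CFUs before and six days", that is, at baseline and on day 6.
- **Threshold on P for every test:** "value ≤0.05 will be considered to be statistically significant".

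The difference follows from the sampling scheme under Procedures and interventions. Every patient is swabbed before the dressing and again when it comes off, which is day 1 in group I and day 6 in group II. In addition, "Additional samples will be obtained on the sixth postoperative day from patients in group I". Both arms therefore have a before and a day-6 sample, and only group I has a day-1 sample. The tests are run separately for each culture medium, and four media are plated.

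**The concern.** The extra swab changes how the shared contrast is judged. In group I, the change from before to day 6 must pass a global test over three times and then a multiple-comparisons procedure. In group II it faces one paired test. The same data could be called significant in one arm and not in the other purely because of the rule.

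The outcome concerned is the primary one, CFUs, and the section does not say which of its CFU tests carries the conclusion. A report of a significant change under the six-day dressing and none under the one-day dressing would invite a reader to credit or blame dressing duration. The rule makes that pattern more likely than its mirror image.

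**Working it through.** **Inputs.** From the documents: 48 patients per arm, threshold 0.05, counts above 300 recorded only as >300. Assumed: two-sided tests and the CFU distribution, which the article does not give. The planned size of 48 cannot be reproduced because no SD is stated. It implies an SD of 100 / [(1.960 + 1.645) × √(2/48)] ≈ 136 CFU. Nothing below depends on this.

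**Step 1: can the gate alone block the contrast?** One simulated set of 48 patients, selected to illustrate the point, gave Wilcoxon P = 0.029 for before against day 6. Adding a day-1 value gave Friedman P = 0.157, so the pairwise step would never be reached. This shows that it can happen, not how often.

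**Step 2: how often?** Log-normal counts (median about 20, between- and within-patient log SD 1.0, capped above 300), day-1 shift half the day-6 shift, 2,000 trials per row. Both rules were applied to the same before and day-6 values. Entries are % significant.

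| Day-6 log shift | Group II rule | Group I, Dunn–Bonferroni | Group I, Bonferroni Wilcoxon | Group I, gate then uncorrected Wilcoxon |
|---|---|---|---|---|
| 0 | 5.2 | 1.7 | 1.1 | 2.0 |
| 0.3 | 22.8 | 12.5 | 9.7 | 13.3 |
| 0.5 | 56.8 | 35.5 | 30.2 | 38.5 |
| 0.8 | 92.1 | 81.1 | 77.0 | 82.7 |

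At a shift of 0.5 the gap is 56.8 − 35.5 = 21.3 points with Dunn–Bonferroni and 56.8 − 30.2 = 26.6 with Bonferroni Wilcoxon. The last column shows that the gate lowers the rate even with no multiplicity correction.

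**Step 3: discordant verdicts between arms.** The arms are independent, so P(II only) = p_II × (1 − p_I). At a shift of 0.5:

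- written plan, Dunn–Bonferroni: 0.568 × 0.645 = 0.366; reverse pattern 0.355 × 0.432 = 0.153
- written plan, Bonferroni Wilcoxon: 0.568 × 0.698 = 0.396; reverse pattern 0.302 × 0.432 = 0.130
- same Wilcoxon in both arms: 0.568 × 0.432 = 0.245 in each direction

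The asymmetry therefore adds about 12 to 15 points to a baseline of about 25%. Negative binomial scenarios with identical modest changes agree. With tie-corrected Dunn or Bonferroni Wilcoxon, the group I rule is significant in about 22-54% of trials and the group II rule in 46-68%. Significance in II only occurs in about 31-41%, against 21-27% with the same Wilcoxon test in both arms. (With a common power p the baseline is p(1 − p), at most 25%; the excess is simulation error.)

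**Step 4: dependence on the post hoc method.** Suppose 7 of 48 patients go from zero to positive by day 6 and everyone is at zero on day 1.

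- Group II rule: exact Wilcoxon P = 2 × 0.5^7 = 0.016 (asymptotic 0.018).
- Group I gate: tie-corrected Friedman P = 0.0009, passed.
- Dunn–Bonferroni ignoring ties: mean-rank difference 1.5 × 7/48 = 0.219; SE = √(12/288) = 0.204; z = 1.07; P = 0.284; × 3 = 0.85.
- Dunn–Bonferroni with tie correction: factor 126/1152 = 0.109; SE = 0.204 × √0.109 = 0.0675; z = 3.24; P = 0.0012; × 3 = 0.0036.
- Bonferroni Wilcoxon: 3 × 0.0156 = 0.047 (exact) or 3 × 0.0180 = 0.054 (asymptotic).

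The same data give about 0.004, 0.05 or 0.85 in group I. With the tie correction, group I has the smaller P value of the two arms.

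**The case against.** Friedman for three related samples and Wilcoxon for two is the conventional choice for this sampling scheme, and neither test is wrong. More importantly, the article plans a direct between-group test, Mann–Whitney at day 6, with the same statistic and threshold for both arms. Nothing says that the arms will be compared by setting two within-arm verdicts side by side. If both arms change identically from randomised baselines, the day-6 test shows a difference only at its error rate and would contradict the misreading. This stands, and it limits the point to reporting and interpretation.

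Three stronger readings are tempting but not supported:

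- **That the trial's answer on dressing duration is biased.** The randomised comparison does not pass through either within-arm procedure.
- **That 30-62% of trials would show significance in group II only because of the asymmetry.** Figures of that size arise with a Dunn standard error that ignores ties, and they leave out the 21-27% discordance expected with identical tests.
- **That sparse media suffer most.** This rests on the same uncorrected standard error. With tie correction, the II-only share was 35-40% for means of 0.1-1 and 35-36% for means of 5-40.

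Nor is the direction guaranteed. On the same log-normal data, significance by the group I rule alone occurred in 1-2.5% of trials with shifts of 0.3-0.8 (Dunn–Bonferroni). With heavy-tailed data it occurred in 5-7%, and in one such scenario the two rules had equal rates (72.6% and 72.3%).

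Using the same test in both arms also leaves the baseline discordance in place. That is true, and it is why the fix needs a statement on interpretation as well as a change of test.

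**Conclusion.** The point holds as a matter of limited importance that is cheap to put right. For identical modest changes, the group I rule is typically harder to pass by roughly 10 to 30 percentage points, and at about 2% against 5% when nothing changes. This adds something like 10 to 16 points to the chance of a result significant in group II only.

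These sizes rest on assumed negative binomial or log-normal counts, two-sided tests and a choice of post hoc method that the article does not name. They shrink for large changes: with a mean rising from 5 to 80 CFU, both rules reach 100%. Heavy tails or heavy ties can remove or reverse the gap. The gate and the different tests are explicit in the article, and the gate alone lowered the group I rate in these simulations. The day-6 Mann–Whitney comparison is untouched.

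**What to change.** In the Statistical analysis section:

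1. Test before against day 6 with the same Wilcoxon signed-rank test at the same significance level in both arms, for each medium.
2. Report each arm's paired change with a confidence interval, treating counts recorded as >300 alike in both arms.
3. Keep the Friedman test and its multiple comparisons only to describe the additional day-1 time point in group I.
4. State that conclusions about dressing duration rest on the between-group Mann–Whitney comparison, not on contrasting within-arm P values.

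The cost is a few sentences of wording and one extra paired test per medium in group I, with no new data. The downside is one more within-arm P value per medium in that arm, which item 4 keeps in its place. The Trial status section reports 69 of the planned 96 patients enrolled, so at that stage the wording could still be settled before the final analysis.

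### The day-6 between-arm CFU comparison is valid but ignores each patient's pre-dressing count, and so may give up precision that costs nothing to recover

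*Protocol article*

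**What the plan says.** All references are to the protocol article.

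- **The count exists for everyone.** Procedures and interventions: "A sample of skin flora will be obtained for semiquantitative culture before the application of a dressing over the surgical incision".
- **It precedes the allocation.** Same section: "On the first postoperative day, the allocation envelopes will be opened". Until then the surgical team does not know the arm, so the arm cannot influence the pre-dressing count.
- **The skin has just been prepared.** Before that swab, "antisepsis of the surgical site will be performed with a 0.5% chlorhexidine solution in alcohol", and "The surgical site will be cleaned with sterile saline after the surgery".
- **How the count is used between arms.** Statistical analysis: the Mann–Whitney test is to "compare groups I and II in terms of the number of CFUs before and six days after the application of the dressing", separately for each medium.
- **How it is used within arms.** For group I, "The Friedman test will be used to compare the number of CFUs in the samples collected before, and one and six days after" the dressing. "In group II, the Wilcoxon test will be used to compare the number of CFUs in samples collected before the dressing" and at day 6.
- **Other baseline tests.** The Mann–Whitney test is also to "test the homogeneity of the groups in terms of age, BMI and duration of surgery". No action is attached to the result of any baseline test.

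No adjusted, change-based or stratified between-arm comparison is named. The section on group assignment describes no stratification by starting count.

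**The concern.** The primary outcome is the CFU count, and the trial measures it on the same media before the arms can diverge. Such a measurement is the natural covariate for the day-6 comparison. Here it feeds only a between-arm test of itself and two within-arm tests.

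The between-arm baseline test cannot help. With allocation random and unrevealed until day 1, any difference it finds is chance, and finding one does not correct the day-6 contrast. The same holds for age, BMI and duration of surgery, which are all settled before the envelope is opened. The within-arm tests do not compare the arms.

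At stake is some precision in a trial of 96 patients, and a day-6 estimate that carries along whatever difference in starting flora chance produced.

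**Working it through.** **1. Inputs.** From Sample size: a difference of 100 CFU per plate, 95% power, 5% alpha, 48 per arm. From Method of sample collection: four media, and counts above 300 recorded only as such. Not given: the SD, whether the test is one- or two-sided, and r. So r is shown as a range.

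**2. The plan's own figure.** Without an SD, 48 per arm cannot be reproduced forward. Solving the usual two-sample formula backward, two-sided:

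SD = 100 × √(48/2) / (1.960 + 1.645) = 100 × 4.899 / 3.605 = 135.9 CFU.

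One-sided, the same step gives 148.9. The value 135.9 serves below only as a scale.

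**3. Precision.** Linear adjustment multiplies the residual variance by 1 − r². At r = 0.3, n per arm is 48 × 0.91 = 43.7, so 44. Power at 48 per arm is Φ(3.605/√0.91 − 1.960) = Φ(1.819) = 96.6%.

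| r | variance reduction | n per arm for 95% power | power at 48 per arm, 100 CFU | power at 48 per arm, effect with 80% unadjusted power |
|---|---|---|---|---|
| 0 | 0% | 48 | 95.0% | 80.0% |
| 0.1 | 1% | 48 | 95.2% | 80.4% |
| 0.2 | 4% | 47 | 95.7% | 81.6% |
| 0.3 | 9% | 44 | 96.6% | 83.6% |
| 0.5 | 25% | 36 | 98.6% | 89.9% |
| 0.7 | 49% | 25 | 99.9% | 97.5% |

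**4. Chance imbalance.** The standard error of a baseline difference, in SD units, is √(2/48) = 0.204. A difference of 1.96 standard errors is therefore 0.40 SD. The expected shift in the unadjusted day-6 difference is r × 0.40 × 135.9, or about r × 54 CFU. That is 5 CFU at r = 0.1, 16 at 0.3 and 27 at 0.5, against a target of 100.

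**5. Does this carry over to ranks, a ceiling and a floor?** The factor 1 − r² belongs to linear models, so the planned Mann–Whitney was simulated against Quade's rank ANCOVA. Assumptions: 48 per arm; log-normal counts with log SD 1.5; day-6 median 80; counts capped above 300; an arm shift of 0.6 SD on the log scale; r defined on that scale. The baseline median was either 30 (few zeros) or 0.3 (about 80% zeros). There were 3,000 runs per setting with an effect and 4,000 without.

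| r | few zeros: Mann–Whitney / adjusted | about 80% zeros: Mann–Whitney / adjusted |
|---|---|---|
| 0 | 0.78 / 0.78 | 0.79 / 0.79 |
| 0.3 | 0.77 / 0.81 | 0.77 / 0.79 |
| 0.5 | 0.77 / 0.87 | 0.79 / 0.83 |
| 0.7 | 0.78 / 0.95 | 0.78 / 0.87 |

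With no effect, rejection rates lay between 0.044 and 0.059 over both tests. In no setting did the two tests differ by more than 0.008.

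**The case against.** The strongest reply is that nothing here is an error. The unadjusted Mann–Whitney test is valid in a randomised comparison, and its error rate already allows for chance imbalance. That stands. A reader might infer from the unadjusted imbalance that the day-6 result is biased; the plan does not support that reading. A shift of r × 54 CFU is ordinary sampling variation that adjustment would reduce.

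Second, the gain may be close to nil. The baseline swab follows chlorhexidine antisepsis and saline cleaning, so many counts may be zero and r may be weak. At r of 0.2 or less, at most one patient per arm is saved. Even at r = 0.5, power for the 100 CFU target rises only from 95.0% to 98.6%; the larger gains concern smaller effects. This also stands, and it limits how strongly the point can be put.

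Third, four media with possibly sparse counts could make an ordinal regression unstable. That is a good reason to choose a rank method with a stated fallback. It is not a reason to leave the baseline unused.

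Fourth, an analysis plan that is not shown might add an adjusted analysis. It might, but the article itself names the between-arm test, and the point is about that stated choice.

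**Conclusion.** The point holds as a missed efficiency. The planned day-6 test is valid, but it leaves out a covariate that is already collected and cannot be affected by arm. The approximate variance reduction is 0–4% for r up to 0.2, 9% at 0.3 and 25% at 0.5. With mostly zero baselines the simulated power gain was smaller: 0.77 to 0.79 at r = 0.3, and 0.79 to 0.83 at r = 0.5. At r = 0 the simulated adjustment cost essentially no power.

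Two stronger readings are not supported:

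- **That precision is certainly lost.** The documents give no correlation and no baseline distribution, so the loss is only possible.
- **That the baseline tests carry about a 30% risk of a false imbalance.** Seven tests (age, BMI, duration and four media) give 1 − 0.95⁷ = 0.30 only if they are independent, and the four plates are aliquots of one swab. As no decision hangs on these tests, a false positive would not change the planned day-6 analysis. The objection to them is that they are uninformative.

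The figures rest on the back-solved two-sided SD, the assumed values of r and the simulated count distributions. They also assume that the patients analysed are those randomised.

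**What to change.** Change the Statistical analysis wording as follows:

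1. **Main day-6 comparison, for each medium.** Use one rank ANCOVA by Quade's method. Rank day-6 CFU over both arms, with all counts over 300 tied at the top. Rank pre-dressing CFU on the same medium in the same way. Regress the first ranks on the second and compare the residuals between arms.
2. **Sensitivity and fallback.** Keep the unadjusted Mann–Whitney test as a sensitivity analysis. Make it the main test for any medium where nearly all counts are zero, with that threshold fixed in advance and judged on counts pooled over arms.
3. **Baseline.** Drop the between-arm P values for age, BMI, duration of surgery and pre-dressing CFU. Show these variables by arm in a descriptive table.

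The cost is wording only: no new samples, visits or patients, and the method needs nothing beyond ranking, linear regression and a two-group comparison. Trial status reports 69 patients enrolled, so the change should be dated and fixed before counts are examined by arm. Adjusting only after a significant baseline test would be a data-driven choice.

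### No primary medium is named among four separate day-6 between-arm tests at P ≤ 0.05, so the single 5% alpha behind the sample size is not protected

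*Protocol article*

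**What the plan says.** The Outcomes section reads: "The primary outcome will be cutaneous colonization, expressed as the number of CFUs". It does not say on which medium the colonies are counted.

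Under Method of sample collection, each swab is cultured on four media: hypertonic mannitol agar for staphylococci, blood agar for hemolytic colonies, eosin-methylene blue (EMB) agar for Enterobacteriaceae, and Sabouraud agar with chloramphenicol for fungi. Each sample therefore gives four CFU counts.

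The Statistical analysis section plans a Friedman test over three times in group I, a Wilcoxon test over two times in group II, and Mann–Whitney tests between the groups before the dressing and at day 6. It then says: "Tests will always be applied independently for each medium used". One threshold, P ≤ 0.05, applies to everything.

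The Sample size section takes one difference, "an increase in bacterial growth of 100 colony-forming units (CFUs) per plate will be considered clinically significant", and one error rate: "For a statistical power of 95% and an alpha test risk of 5%, the sample size has been estimated to be 48 patients" in each arm. It does not say which plate the 100 CFU refers to. No section of the article gives a primary medium, a hierarchy, an adjustment, or a rule that all media must agree.

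**The concern.** The trial is sized as if there were one primary test at 5%, but the analysis section sets up four between-arm tests of the primary outcome, each at 5% and all of equal standing. Followed as written, the plan lets a chance result on any one of the four media be presented as the trial's positive finding. The article hopes its results will help standardize wound care after this operation, so the claim that a false positive could support is a practical one.

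The within-arm Friedman and Wilcoxon tests are listed alongside the between-arm test without being ranked below it. They do not test the effect of dressing duration, which is the stated aim.

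**Working it through.** **1. Which tests bear on dressing duration.** The plan has four kinds of test, each run on four media:

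- Friedman, group I, three times: within-arm, so it does not compare durations.
- Wilcoxon, group II, two times: within-arm, likewise.
- Mann–Whitney before the dressing: a baseline check, because the envelope is opened only on the first postoperative day.
- Mann–Whitney at day 6: compares the durations.

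That is 4 × 4 = 16 tests, of which only the four day-6 Mann–Whitney tests address the randomized question. Group II has no day-1 sample, so day 6 is the only time after allocation at which both arms are sampled. The multiplicity that matters is therefore four tests, one per medium.

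**2. The plan's own figure.** The 48 per arm cannot be reproduced, because the article gives neither a standard deviation (SD) nor the sidedness of the test. Solving backwards under a two-sided normal approximation (an assumption):

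SD = 100 / [√(2/48) × (1.960 + 1.645)] = 100 / (0.2041 × 3.605) ≈ 135.9 CFU.

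Rounding up to 48 allows an SD from about 134.5 to 135.9, which is a standardized difference d = 100/SD of about 0.74. On a one-sided reading the SD would be about 147.4 to 148.9. The error-rate result in step 3 does not depend on any of this.

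**3. Family-wise error of the four day-6 tests, each at 0.05, with no true difference on any medium.**

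- Independent media: 1 − 0.95⁴ = 1 − 0.8145 = 18.5%. The Bonferroni upper bound is 4 × 0.05 = 20%.
- Equally correlated media (simulation of four two-sided z-tests, 1,000,000 replicates per value; the correlations are assumptions):

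| Correlation | Family-wise error |
|---|---|
| 0.3 | 17.4% |
| 0.5 | 15.6% |
| 0.7 | 13.0% |
| 0.9 | 9.4% |
| 1.0 | 5.0% |

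- Sparse growth: an illustrative Mann–Whitney simulation (4,000 replicates) used two media with 90% zero counts, two with 10% zeros, underlying correlation 0.5, and all counts above 300 tied. It gave 15.4%.

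The rate returns to 5% only when the media are perfectly correlated.

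**4. What a repair costs in power.**

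- Naming one medium keeps alpha at 5% and leaves the planned power and sample size unchanged.
- Bonferroni over four media tests each at 0.05/4 = 0.0125 (two-sided critical value 2.498). With SD 135.9, power = Φ(3.605 − 2.498) = Φ(1.107) ≈ 86.6%. With SD 134.5 it is 87.4%, and a t-test calculation at d = 0.743 gives 86.1%.
- Keeping 95% power at 0.0125 would need about 63 to 64 per arm instead of 48.

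**The case against.** The best defence is that this is a condensed article and that multiplicity adjustment is often left to a separate analysis plan. Testing the media independently may mean only that their counts are not pooled, and no sentence says that one significant medium is enough. If all four media had to be significant, the 5% would be held. It is also fair that four plates from one swab are probably correlated, so 18.5% is the independence value and should not stand as the single estimate.

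The point about correlation stands, which is why a range is given. The point about condensation does not remove the problem. The article states a rule (separate tests per medium at 0.05), and which measurement is the primary outcome is a protocol matter. A later plan could repair this only by changing or adding to what is stated here.

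A reader might infer three stronger criticisms, and the document supports none of them:

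- *That 16 competing tests erode alpha.* Twelve of the 16 are within-arm tests or baseline checks and do not test dressing duration.
- *That the time point is open in any way that matters.* It is not formally labelled primary, but day 6 is the only usable between-arm time after allocation.
- *That discordant within-arm results will be read as a dressing effect.* Nothing says so, and the between-arm test is provided. A figure for how often the arms would disagree needs independent tests of equal power. A three-time Friedman test and a two-time Wilcoxon test give no basis for assuming equal power.

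**Conclusion.** The concern holds for the undefined medium. The primary outcome is tested between arms on four media at P ≤ 0.05 each, with none designated primary and no multiplicity rule, while the sample size assumes one test at 5%. If any one significant medium counts as success, the family-wise error lies above 5% and reaches 18.5% under independence. It is about 9% to 17% for assumed correlations from 0.9 down to 0.3. The document gives no correlation, so no single value can be claimed.

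The 86–87% power under Bonferroni is conditional on a two-sided test and on d of about 0.74, which was back-solved and is not stated in the article. It also comes from normal or t-test formulas, whereas the plan uses a Mann–Whitney test on counts recorded only as above 300 beyond that limit.

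**What to change.** Before any unblinded look at the cultures, amend the Outcomes and Statistical analysis sections as follows:

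- Name one confirmatory test: group I versus group II at day 6, Mann–Whitney, on one medium, two-sided 5%.
- Choose the medium. The mannitol plate is the natural candidate, because the cited six-day result in breast reduction concerned coagulase-negative staphylococci and the Discussion attributes many implant-related infections to Gram-positive cocci. The choice is the investigators'. If they take mannitol, they should say whether the primary count is all staphylococci or the coagulase-negative ones, since the laboratory will separate them: "Staphylococci will be identified as coagulase-negative staphylococci" or *S. aureus*.
- State in the Sample size section that the 100 CFU refers to that plate.
- Report the other three media as secondary, with Holm adjustment among them.
- Label the Friedman, Wilcoxon and pre-dressing comparisons as descriptive, and say that they do not support a claim about dressing duration.

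The cost is a few lines of text, with no extra patients and no loss of power. The downside is that an effect confined to another medium becomes a secondary finding. If the investigators want all four media on an equal footing, they need an adjusted threshold and must accept the power loss or the larger sample shown above. The article reports 69 of the planned 96 patients already enrolled, so the amendment should be dated and made while the group comparison is still unseen.
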